**Locality of the study:**

**Amager & Hvidovre Hospital, Department of Cardiology-253, [name]. Denmark**

## Background

Atrial fibrillation (AF) is the most common cardiac arrhythmia and is often described as the new epidemic among heart diseases (1). In 2010 the estimated worldwide numbers of men and women with AF were 20.9 million and 12.6 million, respectively, with higher incidence and prevalence rates in the developed countries (2). In Denmark, the prevalence of AF is approximately 93,000 and the incidence about 20,000 new cases per year (3). Estimated number AF-patient in local department is 400/ year.

AF is a costly public health problem with hospitalizations as the primary expenditure (4). The disease and treatment is complex and requires a high degree of adherence to prevent complications (stroke and major bleedings) and the burden of symptoms often leads to poor health related quality of life (HRQOL). The impairment of HRQOL due to AF can be comparable to that observed in patients with heart failure which is due to both the often disabling symptoms of the disease, and the risk of complications such as stroke (5)(6). The consequences of AF are often impairment of physical functioning and mental health (7). A qualitative study by McCabe et al. found that AF patients often are anxious. They have feelings of nonsupport, inadequate self-management counseling, and distress associated with the unpredictable symptoms (8).

Illness is considered to be a family affair and it is therefore important for patients and their families to have a chance to talk about issues like suffering and coping (9). Families need support and solutions to ensure successful adjustments to adequately cope with a family member with chronic illness (10). Little is known about how families experience to habituate life with AF, their concerns and feelings and their need for support. One study found that the greatest burden to family members of AF patients occur due to disruption in schedule, followed by financial problems, lack of family support and health problems (11). It has also been described how couples where one suffer from AF often experience uncertainty as a common main concern which is rooted in not knowing enough about the disease (12). Studies have shown that health care providers should not only focus on the patient with AF but should take the family into account as well, when managing this condition because the feelings and illness beliefs affect the entire family (13). Future research and intervention should therefore include the whole family.

Hendriks et al. studied the effect of nurse-led care (focused on AF guidelines and patient information) versus usual care for patients with AF. Nurse-led care was superior to usual care in terms of cardiovascular hospitalizations and cardiovascular mortality (14). These findings have generated more attention towards patients with AF and the possibility that they could benefit from specific disease management and rehabilitation similar to programmes used in other chronic cardiovascular conditions such as heart failure and ischemic heart disease (15)(16). However, no clinical guidelines ensure patients and families education to cope with AF. Furthermore, the limited intervention studies are tested in different settings with AF-patients and with different clinical intervention contents. European Society of Cardiology recommend that more research about care for patients with AF are needed and it is likely to require different designs in different healthcare settings (2). More research should focus on testing new intervention models that could benefit patients and their families.

Family focused Nursing (FFN) with reference to the The Calgary Family Assessment model (CFAM) and the Calgary Family Intervention Model (CIFM) used as a theoretical model have been shown to be helpful in nursing interventions supporting patient and family in managing life with diabetes (17). However the efficacy of these models have never been tested in nursing interventions

involving patients with AF and the possible potential still needs to be proved (12) (18). Optimization of quality and coherence of the patient experience are recommended for patients with heart diseases, where patients and families are the center point of care (16). Unfortunately, these visions are not always realized in practice for patients with AF (19). Therefore, more research is needed about how healthcare professionals can involve, support and educate AF-patients and their families. In future studies of FFN a new pilot study about how AF-patients experience the patient course should be taking in to account. The themes were “*Uncertainty as a companion in the process*”, “*To understand what is wrong with me*”, and “*to put the heart at the right place*”(20).

The rising number of patients with AF, the complexity of the disease and treatment, the frequent non-adherence to treatment, the poor QoL, and lack of support for the family demands attention in the management of AF and in how patients and their families cope with the disease. Evidence of the effect of integrating the family in the counselling of patients are in general sparse (21). To facilitate evidence-based knowledge this study is designed to test a health promoting intervention for patients with AF and their families.

### **Aim and research questions**

The aim of the study is to examine how AF- patients and families are influenced by AF and to test if involving family members in a FFN intervention with group education improves outcomes for patients with AF. The aim can be achieved by answering the following research questions.

Study 1: How does family members and AF patients experience family life being affected by AF?

Study 2: How do family members experience life with a family member having AF?

Study 3: Is a short-term educational and family focused support intervention for patients and family members living with AF more effective on quality of life than standard care?

### **Method**

The study will consist of three sub-studies. A qualitative explorative study with family unit interviews, focus group interview with members of the family, and a quantitative fidelity study evaluating the effect of a family focused nursing intervention based on CFAM and CIFM

### **Materials**

Inclusion criteria: Men and women > 18 years with newly diagnosed AF (< 4 weeks since diagnose) documented in the patient file and verified by a EKG. Family members must be > 18 years old and defined by the patient: e.g. spouse, son, daughter, near friend or neighbor.

Exclusion criteria: Patients with chronic heart failure according to international guidelines (2).

### **Study part 1: Family unit interviews**

Qualitative data with patients and family members will be collected from a semi-structured interview-guide founded in a structured literature search. Families will be recruited using a purposeful sampling strategy. This method is used to find participants who collectively provide a

rich and varied data material. (e.g. difference in gender, age, income, and symptoms). The family interviews will continue until data saturation has been achieved (22) which is estimated to be approximately 15-20 patients including family members. Families will be interviewed at home or at the hospital according to their preferences. A qualitative methodological approach employing Giorgi's descriptive phenomenological method will be used to collect and analyse data which follows four steps 1: The data is read to give an overall impression. 2: Meaningful units are identified. 3: Meaningful units are transformed into categories. 4: Categories are synthesised into the essence of the phenomenon. The researcher's disciplinary perspective and professional sensitivity will guide the process (23) and the researchers preunderstanding will be revealed by a peer interview prior to the data collection. The study will broaden the perspective of how the family are influenced by AF, their thoughts and feelings can be used as inspiration in the intervention study and benefit in how to support AF patients in clinical health care.

### **Study Two: Focus group interviews with family members**

Data will be collected from 2 - 3 focus group interviews each with approximately 5-8 family members. Focus group interviews can be helpful when facilitating the perspectives and opinions of the family members (24). The motive is to attain a condensed and broad description of a phenomenon (25) (26) and to bring positive dynamics into the focus groups, which can help informants to talk about feelings regarding their experiences of being part of a family where a family member has AF. Interview data will be recorded and transcribed ad verbatim and will be analyzed with qualitative content analysis (21). Content analysis is a research method widely used in health care research and it is known for making replicable and valid conclusions from data to their context, with the purpose of providing knowledge, new insights, a representation of facts and a practical guide to action (26).

The gathered knowledge from study 1 and 2 will be used to test the fidelity of a health promoting intervention for AF patients and their families.

### **Study three: Fidelity study**

The fidelity study is designed as a randomized clinical trial. Based on sample-size calculation 100 patients will be allocated in two groups by a computer program. An intervention group (n=50), and a control group (n=50), respectively. The intervention group will receive health promoting group education and sessions based on the theoretical framework of FFN including CFAM and CFIM as a supplement to conventional care and treatment according to international guidelines (2). The interventional focus is on the psychological and educational needs of patients with AF and their families (e. g medication, handling of symptoms, managing stress and anxiety, facilitating the lifestyle changes, exercising, returning to work, and taking part in family and social activities)(27).

The control group will receive conventional care and treatment according to guidelines (2). Conventional care is characterized by ad hoc management as per usual standards of clinical care in Denmark (with access to routine medical care, hospital care, and pharmacotherapy). Patients will be assigned to the fidelity study according to the described in- and exclusion criteria.

The intervention will take place in the Department of Cardiology at Amager Hvidovre Hospital (AAH) and the inclusion period is estimated to one year.

### **Description of the intervention:**

In FFN based on CFAM and CIFM the whole family is considered the unit of assessment and intervention when a member of the family becomes ill (28). In FFN the focus is therefore not only on the patient but on the interaction and the reciprocity between family members, patient and between the nurse. FFN is operationalized within a therapeutic relationship and conversations between a patient / family and a nurse. The idea is to soften illness suffering by creating a context for changing the perspective on illness beliefs and facilitating beliefs that can strengthen the psychological resilience (29). To guide the patient and the families the Family Strength Orientated Therapeutic Conversations (FAM-SOTC) will be used as health promoting conversations and a way to enhance family health (28). The therapeutic conversations build on different theories: System theory, change theory and communication theory. Focusing on illness narrative, therapeutic questions, strengths, identification on psychological endurance and resources and through evidence-based information and recommendation (10).

First part of the intervention is a two hour group session designed by the PhD student and the project nurses based on clinical guidelines of AF-management (2) and theory from multifamily group intervention (30). Nurse specialists will facilitate knowledge to patients and family members about AF and how to support self-management in their daily living. Furthermore during six months' patients in the intervention group will receive 3-5 FAMT SOCT sessions of 30-60 minutes. First session will start as soon as possible and the nurse, patient and family will plan the numbers and session intervals according to the patient and the family needs of support and guidance. The PhD student and two project nurses from the ward will be trained theoretically and practically in performing health promoting family conversations at Linné University in Sweden.

### **Study design, study outcomes, and statistical methods**

To assess the fidelity of the study, a process evaluation will be carried out (31). This will be done by recording all nursing sessions. It will be used to evaluate if the planned intervention is carried out as intended. Process evaluation is very suitable to evaluate the process and to give an estimate of the fidelity of the intervention. It can also explain reasons for success and failure in outcome results (31).

The influence of the intervention is measured quantitatively using internationally validated questionnaires. Measurements of the effect will be collected 24-48 hours after enrollment and follow-up will be made by telephone interviews after 6 months. RedCap database will be used for collecting data and storing data from questionnaires.

The primary outcome is Quality of Life living with AF. This will be accessed with the Atrial Fibrillation Effect on Quality-of-Life (AFEQT) Questionnaire (32). Secondary outcomes of interest are family function which will be measured with the Ice Expressive Family Functioning Questionnaire (ICE-EFFQ) and the Ice Family Perceived Support (ICE-FPSQ) (33). Anxiety scores will be measured with the Hospital Anxiety Depression Scale (HADS) (34), AF symptoms measured with the EHRA scale (European Heart Rhythm Association) (35) and number of hospital admissions registered from The National Patient Registry.

Baseline data will be compared between the intervention group and the standard care group. For demographic data Pearsons  $\chi^2$ -test or Fisher's exact test will be used. Depending on the distribution the independent t-test or Wilcoxon rank-sum test will be used. Normally distributed data will be presented with a mean and a standard deviation (SD), non-parametric data with median and inter quartile range. It is estimated that a sample size of 50 patients in two arms (100 patients total) will

make it possible to detect a difference of 11 points on the AFEQT (36) with a power of 80 % and a significance level of 0.05. Calculation are based on a two-sided independent two-sample t-test. An increase between 6 and 19 points has been suggested to correspond to a meaningful improvement in Quality of life measured on AFEQT (36).

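### Baseline differences between randomised arms are to be significance-tested, and the t-test-or-Wilcoxon rule does not say whether it governs AFEQT, which was sized on a t-test

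*Protocol*

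**What the plan says.** All the relevant text is in the Protocol, section *Study design, study outcomes, and statistical methods*. In order:

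- On timing: "Measurements of the effect will be collected 24-48 hours after enrollment and follow-up will be made by telephone interviews after 6 months".
- On baseline: "Baseline data will be compared between the intervention group and the standard care group". For demographic data the tests are Pearson's chi-square "test or Fisher's exact test will be used".
- Directly after that: "Depending on the distribution the independent t-test or Wilcoxon rank-sum test will be used". The sentence names no variable, no time point and no criterion for judging the distribution.
- On presentation: "Normally distributed data will be presented with a mean and a standard deviation (SD), non-parametric data with median and inter quartile range".
- On size, the claim for 50 patients per arm: "make it possible to detect a difference of 11 points on the AFEQT (36) with a power of 80 % and a significance level of 0.05". The basis is a two-sided independent two-sample t-test. No SD is given. A rise of 6 to 19 points is mentioned as a suggested range for meaningful improvement.

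The section *Study three: Fidelity study* says that the 100 patients are randomised by computer, 50 to each arm. No sentence in the protocol assigns a test or effect measure to AFEQT at 6 months.

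**The concern.** There are two separate issues.

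**Baseline tests.** With computer allocation, the null hypothesis of a baseline significance test is true by design. The p-value cannot measure whether an imbalance matters for the outcome. A p-value below 0.05 is a chance event, and one above 0.05 does not show that a prognostic variable is balanced.

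**Scope of the t-test/Wilcoxon rule.** It is the only analysis rule for continuous variables in the document, and it stands just before the sample-size text for the primary outcome. A reader cannot tell whether it applies to AFEQT. If it does, the observed data decide whether the primary result is a mean difference or a rank comparison reported with medians. The trial was sized for the mean difference, so the reported quantity could differ from the one that justified 100 patients.

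**Working it through.** **1. The plan's own figure.** Inputs from the protocol: difference 11 points, power 80%, two-sided alpha 0.05, 50 per arm, two-sample t-test. With no SD stated, the sample size cannot be reproduced forwards, so I solved for the SD it implies.

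- t-test: the detectable standardised difference at 50 per arm is 0.566, so SD = 11 / 0.566 = 19.4.
- Normal approximation: SD = 11 / [(1.96 + 0.84) × √(2/50)] = 19.6.

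The target is therefore a mean difference of 11 AFEQT points with an SD of about 19.4.

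**2. Baseline tests.** The chance of at least one p < 0.05 among k independent variables under correct randomisation is 1 − 0.95^k. The protocol gives no k. For an assumed k = 10 it is 1 − 0.95^10 = 0.40; for k = 20 it is 1 − 0.95^20 = 0.64.

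**3. Type I error if the rule covers AFEQT.** Simulations used 50 per arm. The score distributions are assumptions, and so is the switch (Shapiro-Wilk at 0.05 in each arm), because the protocol states no criterion.

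| Procedure under the null | Type I error |
|---|---|
| t-test always (skewed scores, mean 70, SD 19.4) | 5.2% |
| Wilcoxon always (same scores) | 5.0% |
| Switch on normality test (same scores) | 5.2% |
| Switch on normality test (normal, Beta(3,1), Beta(4,0.9)) | 4.9 to 5.2% |
| Smaller of the two p-values (all the above distributions) | 6.0 to 6.7% |

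With the skewed mean-70 scores, the switch chose Wilcoxon in about 92% of null trials and in nearly all trials with means 70 and 81. If AFEQT scores are that skewed, the test used for sizing would seldom be the one applied.

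**4. Power if the rule covers AFEQT.**

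| Assumed scenario | t-test | Wilcoxon |
|---|---|---|
| Normal, SD 19.4, 11 points (separate runs) | 79 to 81% | 78 to 79% |
| Beta(4,0.9) vs Beta(2.2,0.9), SDs 15.9 and 22.4, about 10.7 points | 78% | 68% |
| Skewed, means 81 and 70, SDs 17 and 19.4 | 85% | 89% |
| Pure 11-point shift of Beta(2.2,0.9), not capped at 100 | 68% | 74% |

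Neither test is better throughout. The two disagree on significance in about 5% of trials in the first scenario and about 12% in the second.

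**5. What a fixed, baseline-adjusted analysis gives.** For ANCOVA with baseline-to-6-month correlation ρ, the residual SD is 19.44 × √(1 − ρ²), and by normal approximation power = Φ[11 / (residual SD × √(2/50)) − 1.96]. For ρ = 0.5: residual SD = 16.83; 16.83 × 0.2 = 3.37; 11 / 3.37 − 1.96 = 1.31; Φ(1.31) = 0.90.

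| Assumed ρ | Residual SD | Power, 50 per arm | n per arm for 80% |
|---|---|---|---|
| 0 | 19.44 | 0.81 (0.80 by exact t-test) | 50 |
| 0.3 | 18.54 | 0.84 | 45 |
| 0.5 | 16.83 | 0.90 | 37 |
| 0.7 | 13.88 | 0.98 | 26 |

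**The case against.** The strongest reply is that the t-test/Wilcoxon sentence belongs to the baseline paragraph. It follows the baseline comparison and the tests for demographic data, so its natural scope is continuous baseline variables. This stands. A reader might infer that the primary comparison is left to be chosen from the data; the text does not say so, and that is only one reading. On the baseline-only reading, what is left is that no test is named for 6-month AFEQT. That is commonly left to a statistical analysis plan, which may exist here, so its absence is not raised as a fault.

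Other inferences also go too far:

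- *That these are the only tests in the plan.* A two-sample t-test is named for sizing, and it is the one test the document ties to AFEQT.
- *That type I error is inflated.* The 6.0 to 6.7% arises only if the smaller p-value is picked. The protocol says the choice depends on the distribution, and a switch of that kind stays near 5%.
- *That Wilcoxon costs ten points of power.* That is one skewed scenario with unequal SDs; in others the gap is small or reversed.
- *That the result would no longer be in AFEQT points.* Medians and a Hodges-Lehmann shift remain in points. What is lost is the mean difference.
- *That 6 to 19 points is a decision threshold.* It is cited only as a suggested range of meaningful improvement.
- *That baseline p-values will drive covariate choice.* No such use is planned, and no stated conclusion depends on them.

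**Conclusion.** The point holds in a limited form. Significance tests of baseline differences between randomised arms are planned and are uninformative; this is certain from the text but minor. The scope of the t-test/Wilcoxon rule is unclear, and if it reaches AFEQT it is inconsistent with a sample size built on a t-test for an 11-point mean difference. That second part is conditional on a reading which the document neither confirms nor excludes.

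The harm is to pre-specification and interpretation, not to error control. The reason to act is that the remedy is nearly free and brings a gain: power for 11 points of about 0.84 to 0.98 in place of about 0.80. This rests on the implied SD of about 19.4 and on assumed correlations of 0.3 to 0.7, neither of which the protocol states, and on all 50 patients per arm being analysed.

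**What to change.** Make three changes in *Study design, study outcomes, and statistical methods*:

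1. Describe baseline data by arm with means and SDs, medians and interquartile ranges, or counts, without p-values.
2. State that the t-test/Wilcoxon rule does not govern the primary outcome.
3. Name the primary analysis as the difference between arms in mean AFEQT at 6 months, adjusted for baseline AFEQT (ANCOVA), with a 95% CI, whatever the observed distribution. Keep any rank test as a sensitivity analysis.

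The cost is a few sentences, with no extra patients or visits, since AFEQT is already collected at both times. One condition needs confirming: the baseline AFEQT must be completed before the intervention starts. The protocol takes it 24 to 48 hours after enrolment, while *Description of the intervention* has the first session begin as early as possible, and the order of the two is not stated.

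### The AFEQT sample size rests on an unadjusted t-test and only unadjusted tests are named; adjusting for the AFEQT score already collected at enrolment would be a free gain in precision

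*Protocol*

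**What the plan says.** All of the statistical text is in the Protocol section 'Study design, study outcomes, and statistical methods'.

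- **Outcome and timing.** "The primary outcome is Quality of Life living with AF", measured with AFEQT. "Measurements of the effect will be collected 24-48 hours after enrollment and follow-up will be made by telephone interviews after 6 months". An early and a 6-month score are therefore planned for each patient.
- **Tests named.** The analysis text opens with a comparison of baseline data between the arms, gives chi-squared or Fisher's exact tests for demographic data, and continues: "Depending on the distribution the independent t-test or Wilcoxon rank-sum test will be used". No baseline-adjusted model appears anywhere.
- **Sample size.** 50 patients per arm are said to be enough for a difference of 11 AFEQT points "with a power of 80 % and a significance level of 0.05". The basis is given as: "Calculation are based on a two-sided independent two-sample t-test". The section 'Study three: Fidelity study' repeats the numbers: "An intervention group (n=50), and a control group (n=50), respectively".

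The protocol does not give the SD behind the calculation, the correlation between early and 6-month AFEQT, an allowance for dropout, or whether the 11 points refer to the 6-month score or to the change from the early score.

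**The concern.** The early score on the primary outcome is normally the strongest single predictor of the later score. An unadjusted comparison leaves the variance it would explain in the standard error. It also leaves part of any chance difference between the arms at the start in the estimate. The only use of baseline data that the protocol states, a between-arm comparison, neither improves precision nor corrects for imbalance.

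This matters more here because the margin is thin. The calculated number equals the number to be randomised, so any patient lost before the 6-month telephone follow-up takes an unadjusted test below its nominal 80%. Baseline adjustment could restore some or all of that with data the trial already plans to collect.

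**Working it through.** **Inputs from the protocol:** difference 11 points; n = 50 per arm; two-sided alpha 0.05; power 80%; independent two-sample t-test.

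**Inputs that are assumptions:** the SD (back-solved below) and the correlation r between early and 6-month AFEQT (shown over 0.3 to 0.7).

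**Step 1. The plan's own figure.** Without an SD, the 50 per arm cannot be reproduced independently. It can only be solved backwards.

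- Normal approximation: SD = 11 / [(1.960 + 0.842) × √(2/50)] = 11 / (2.802 × 0.2) = 19.6.
- Noncentral t with 98 degrees of freedom: SD = 19.44, a standardised difference of 11/19.44 = 0.566.

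The 80% is therefore nominal. At other SDs, unadjusted power at 50 per arm (noncentral t) would be 85.7% (SD 18), 77.7% (SD 20), 69.7% (SD 22) or 58.6% (SD 25). The steps below use 19.44, which reproduces the stated 80%, and take it as the SD of the 6-month score.

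**Step 2. Effect of adjustment.** ANCOVA residual SD = SD × √(1 − r²), with 2n − 3 degrees of freedom and noncentrality 11 / [residual SD × √(2/n)]. For example, at r = 0.5 the residual SD is 19.44 × √0.75 = 16.83 and the noncentrality is 11 / (16.83 × 0.2) = 3.27.

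| Analysis | Residual SD | Power, 50 per arm | Detectable difference at 80% power | Power, 45 per arm | Power, 40 per arm |
|---|---|---|---|---|---|
| Unadjusted t-test | 19.44 | 80.0% | 11.0 | 75.6% | 70.5% |
| ANCOVA, r = 0.3 | 18.54 | 83.6% | 10.5 | 79.5% | 74.5% |
| ANCOVA, r = 0.5 | 16.83 | 89.9% | 9.5 | 86.5% | 82.3% |
| ANCOVA, r = 0.7 | 13.88 | 97.5% | 7.9 | 96.1% | 93.8% |

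The 45 and 40 per arm correspond to assumed losses of 10% and 20%.

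**Step 3. Chance imbalance.** If the early score has the same SD, the standard error of the difference in early means is 19.44 × √(2/50) = 3.9 points, about a third of the 11-point target. With equal variances, an unadjusted 6-month comparison carries a fraction r of any such imbalance. A 3.9-point imbalance at r = 0.5 shifts the estimate by 0.5 × 3.9 = about 1.9 points.

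**Step 4. Score or change.** If 19.44 is the SD of a single-time score, the change has SD 19.44 × √(2(1 − r)). A t-test on change then has 65.8% power at r = 0.3, 80.0% at r = 0.5 and 95.1% at r = 0.7. If instead the 11 points and the unstated SD already refer to change, power is 80% by construction and these figures do not apply. With the early score in the model, the estimated arm difference is the same whether the response is score or change.

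**The case against.** The strongest reply is that the protocol has made no error here. The t-test sentence describes the sample-size calculation, and the other mention of a t-test follows a sentence about baseline comparisons. No sentence fixes the 6-month analysis of AFEQT. The choice of covariates is commonly left to a statistical analysis plan, which may exist and is not shown. Sizing on a t-test is a usual and conservative basis for a trial later analysed by ANCOVA on the follow-up score. The sizes above also depend on an SD and a correlation that the document does not supply.

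All of that stands, and it rules out several stronger readings that a reader might infer:

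- **That the protocol commits to an unadjusted primary analysis.** It names only unadjusted tests, but does not expressly assign one to the 6-month comparison.
- **That the 80% is wrong or the trial underpowered.** If the unstated SD is that of the score compared, an unadjusted test at full follow-up has the stated power.
- **That an early imbalance passes in full into the result.** Only the fraction r does. Under randomisation the t-test is still unbiased, and its standard error already reflects this variation.
- **That a change-score analysis would have about 66% power.** This needs both r = 0.3 and 19.44 being a single-time SD.
- **That allocation is unstratified.** The protocol says only that a computer program allocates patients; stratification is neither stated nor excluded.

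The reply does not reach the recommendation itself. The methods that the protocol does name make no use of the early score, and a better one is available from the same data.

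**Conclusion.** The point holds as a free improvement, not as an error in a stated figure. The AFEQT calculation and the only named tests for continuous data are unadjusted, although an early AFEQT score is to be collected.

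The forgone gain is roughly 4 to 17 percentage points of power at 50 per arm for r between 0.3 and 0.7 (83.6% to 97.5% against 80.0%), and about 11 points at 45 per arm with r = 0.5 (86.5% against 75.6%). These sizes rest on the back-solved SD and the assumed correlations. The direction of the gain does not depend on the exact values, provided the two scores are more than weakly correlated.

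One condition attaches. The early score is taken 24 to 48 hours after enrolment, its order relative to randomisation is not stated, and the section 'Description of the intervention' has the first session begin without delay. If the score were taken after patients knew their arm or had started sessions, it could already carry part of the effect and would not be a sound baseline covariate.

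**What to change.** - State that the primary analysis is a linear model of the 6-month AFEQT score on randomised arm and early AFEQT score, reporting the adjusted mean difference in points with its 95% CI. Keep the t-test as a supportive analysis.
- Use the same model, each with its own early score, for ICE-EFFQ, ICE-FPSQ and HADS.
- State that the early questionnaires are completed before allocation is known and before the first session, or confirm that this is already the practice.
- Next to the sample size, give the SD used and say whether it describes the 6-month score or the change.

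The cost is a few sentences in the protocol or statistical analysis plan. No patients, visits or data items are added. The only possible operational change is the order of the early questionnaire and the release of the allocation, if that order is not already as needed.
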